## Measures

### Online entry questionnaire measures

With the online entry questionnaire, the following sociodemographic control variables will be collected: age, gender, shift work (yes/no), and place of study. Additionally, to determine the eligibility of interested students, the following parameters will be gathered: current enrolment year, previous experiences in BBN, cardiovascular and neuroendocrine diseases, wearing a pacemaker (yes/no), use of medication and psychoactive drugs. Female participants will further provide information on the timing of their menstrual cycle and indicate whether they are pregnant, lactating, or use hormonal contraceptives.

### Experimental session measures

From the measures obtained during the experimental session, we will derive primary outcomes, which will be used for hypothesis testing, and secondary outcomes, which will be used as control variables in the primary analyses or for exploratory analyses.

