Stress mindsets are global belief systems about the nature of stress [86]. Individuals with a stress-is-enhancing mindset belief that stress is positive and promotes health and performance, whereas individuals with a stress-is-debilitating mindset belief that stress is negative and harms health and performance. By assessing stress mindsets before and after the interventions, we can check if the manipulations affected an individual’s perception of stress (e.g., [57]). This is especially interesting for medical students, since they already have a certain understanding of the functionality of stress responses presented in SAR. Pre-existing stress mindsets might be pivotal for the effectiveness of SAR interventions [67]. One previous study suggests that most cognitive benefits occur when an individual holds a stress-is-enhancing mindset and appraises a stressor as challenge [57]. However, one could also argue that instructing individuals with a stress-is-enhancing mindset to reappraise stress arousal as functional is redundant [67]. Therefore, we will (1) consider stress mindset as a control variable in the primary analysis and (2) analyze stress mindset as a secondary outcome, to evaluate if SAR interventions affect the stress mindset of medical students.

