
**Fig. 2 Fig2:**
[figure not shown]
Experimental Session *Note*: Q1 contains the Multidimensional Mood State Questionnaire (MDMQ) and Stress Mindset Measure (SMM). Q2 contains the MDMQ, self-reported demands and resources, prior BBN experience and skills, and BBN interest and motivation. Q3 and Q4 both contain the MDMQ and self-reported demands and resources. Q5 includes the Depression, Anxiety and Stress Scale (DASS-21), Emotion Regulation Questionnaire (ERQ), SMM and MDMQ. Q6 contains the MDMQ

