### Statistical analysis plan

To test the effectiveness of the interventions on communication performance (H1.2, H2.2), we will use 2 (SAR vs. no SAR) x 2 (WE vs. no WE) between-subjects ANOVAs. For the analysis of the repeated psychophysiological stress response outcomes (H1.1, H2.1), we will use linear mixed models with the participants as random effect. To test if the effects of the interventions on communication performance are mediated by the psychophysiological stress response (H3.1, H3.2), we will conduct a bootstrapping mediation analysis following state-of-the-art methodology [101]. We will follow international guidelines to derive the parameters used in the statistical analysis. For each cardiovascular measure, the mean of each 1-minute period will be calculated. For salivary measures, the area under the curve with respect to ground and increase will be computed. Where sensible, we will transform skewed variables to approach normality. We will perform sensitivity analyses with the control variables gender, age, BMI, use of hormonal contraceptives, shift work, SP, stress mindset, depression anxiety and stress, body motion, BBN-related interest & motivation, BBN-related prior experience & skills, and habitual use of emotion regulation strategies. For significance testing, an alpha level of 0.05 will be used.

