### Possible pitfalls

We are aware that the present project is ambitious, which brings several possible challenges.

First, participation in the project will not be part of the regular medical study program but will rather be offered as an extracurricular learning opportunity. Although we assume that medical students have a general interest in communication training, we still rely on voluntary participation.

Second, medical students represent a distinct group of individuals compared to previous SAR-related research. In the third year, medical students already have a solid understanding of the functionality of their stress response, which is a core aspect of SAR interventions. Importantly, a person’s beliefs about stress (i.e., stress mindset) can affect their situation specific stress appraisal [67]. It remains to be seen how the SAR intervention applied in our study will affect the psychophysiology and performance of medical students specifically. We will investigate this issue by assessing participants’ stress mindset before and after the intervention and use it as control variable for primary analyses.

Third, there are more female medical students enrolled in Swiss universities than male students. Gender creates a possible confounder, given the different psychophysiology [87]. To ensure equal allocation to the experimental conditions, participants will therefore be stratified according to gender. Besides, the menstrual cycle of female participants causes monthly fluctuations of steroid hormones, which influence their psychophysiology. To control for these fluctuations, female participants will optimally be tested during the first week after menstruation. This puts restrictions on participation opportunities.

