Lastly, while the BBN scenario is the same for all participants, for feasibility reasons, the SP role will be portrayed by different actors. To minimize any influence from SPs playing their role differently, a professional SP instructor of the Institute for Medical Education will provide detailed and identical training to each SP and ensure comparable acting. Further, SP will be considered as control variable in our statistical analyses. At the same time, because the BBN situation is only simulated, ecological validity could be questioned. Yet, due to the nature of the task, it is not feasible to conduct the experiment with real patients. It has been shown that communication skills performances exhibited in settings with SPs can predict performances in real clinical life [105].

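### Stress mindset is a covariate in the primary analysis in two sections but only in sensitivity analyses in the statistical analysis plan, and no section says which model decides H1 and H2 or which mindset measurement is meant

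*Protocol article*

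**What the plan says.** Three sections connect control variables with the primary analyses.

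- **Hypotheses** (last paragraph): the authors will "consider stress mindset as a control variable in the primary analysis" and, as a separate second item, analyse it as a secondary outcome.
- **Experimental session measures**: the session yields primary outcomes and "secondary outcomes, which will be used as control variables in the primary analyses or for exploratory analyses". No variable or model is named here.
- **Possible pitfalls**: after mentioning that mindset is assessed before and after the intervention, the authors say they will "use it as control variable for primary analyses".

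The **Statistical analysis plan** section reads differently. For communication performance, "we will use 2 (SAR vs. no SAR) x 2 (WE vs. no WE) between-subjects ANOVAs". For the repeated stress outcomes, "we will use linear mixed models with the participants as random effect". Neither sentence names a covariate. Later in the paragraph comes "We will perform sensitivity analyses with the control variables gender, age, BMI, use of hormonal contraceptives, shift work, SP, stress mindset", and the list continues from there.

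Possible pitfalls adds that "SP will be considered as control variable in our statistical analyses", without saying whether primary or sensitivity analyses are meant.

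On timing, the note to Figure 2 places the stress mindset measure in Q1, before the learning phase, and again in Q5, after the learning phase and the BBN task. The DASS-21 and the ERQ appear in Q5 only.

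**The concern.** Stress mindset cannot be both a term in the primary model and a term that enters only in sensitivity analyses. Each test under H1 and H2 therefore has two candidate deciding p-values, and the article does not stop the choice from being made once both are known.

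Stress mindset is an awkward variable to leave in this position. The plan also treats it as an outcome that SAR may change, and it is measured on both sides of the intervention. As a covariate, the Q1 value is harmless. The Q5 value is post-randomisation: if SAR shifts mindset and mindset affects the outcome, adjusting for Q5 takes that part of the effect out of the SAR estimate. The wording in Possible pitfalls mentions both assessments and does not say which one enters the model.

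**Working it through.** **1. The sections side by side.**

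| Section | Variable | Role |
|---|---|---|
| Hypotheses | stress mindset | primary analysis |
| Possible pitfalls | stress mindset | primary analyses |
| Experimental session measures | secondary outcomes, unnamed | primary analyses *or* exploratory |
| Possible pitfalls | SP | statistical analyses, unspecified |
| Statistical analysis plan | stress mindset, SP, gender and others | sensitivity analyses |

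The direct contradiction is rows 1 and 2 against row 5, on stress mindset. Row 3 is looser, and row 4 is undetermined.

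**2. Does the sample size settle it?** Inputs from the sample size section: d = 0.40, two-tailed alpha 0.05, power 0.80, N = 200. Each main effect compares 100 with 100.

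- Normal approximation: n per level = 2 × (1.960 + 0.842)² / 0.40² = 98.1, rounded up to 99, so N = 198.
- F test for a main effect, f = 0.20, df 1 and N − 4: the smallest N is 199, and power at N = 200 is 0.804.

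So 200 reproduces without covariates. That fits the models as the statistical section states them. It does not exclude adjustment: with one covariate of no predictive value, power at N = 200 is still 0.804, and with R² = 0.10 it is 0.843.

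**3. Type I error if either model could be called primary.** The documents give no R² (the share of outcome variance that the covariate explains), so a range is assumed. Under the null, in the 2×2 model with one pre-intervention covariate, the unadjusted and adjusted test statistics are approximately bivariate normal with correlation √(1 − R²). The chance that at least one is significant is 1 − P(|Z₁| < 1.96 and |Z₂| < 1.96).

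| Assumed R² | Correlation | P(either p < 0.05) |
|---|---|---|
| 0.01 | 0.995 | 0.055 |
| 0.05 | 0.975 | 0.060 |
| 0.10 | 0.949 | 0.065 |
| 0.20 | 0.894 | 0.071 |
| 0.40 | 0.775 | 0.080 |

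A simulation at N = 200 (8,000 null trials per setting) agrees: 0.064 at R² = 0.10 and 0.077 at R² = 0.40 with one covariate. With 18 covariates, a number assumed to stand for the full list, it gives 0.068 at R² = 0.10 and 0.084 at R² = 0.40.

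**4. How often the two models disagree at the design effect.** At d = 0.40 the unadjusted statistic has mean √200 × 0.20 = 2.83, and the adjusted one 2.83 / √(1 − R²). With one covariate, the same bivariate normal calculation gives opposite verdicts in about 2% of trials at R² = 0.01, 5% at 0.05, 7% at 0.10 and 16% at 0.40. At R² = 0.10 the adjusted model alone is significant in 5.6% and the unadjusted model alone in 1.7%.

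**5. Limits.** Steps 3 and 4 concern a main effect in the 2×2 model with pre-intervention covariates. The mixed models for the repeated outcomes were not checked.

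**The case against.** The best defence is that the statistical analysis plan section governs. It is the only section that names models, it assigns them to hypotheses, it describes the covariate runs separately as sensitivity analyses, and the sample size matches models without covariates. The Hypotheses section only says that mindset will be considered. This is a sensible way to read the article, but the article does not state it, and Possible pitfalls says without qualification that mindset is used in the primary analyses. Nor is this detail left to a fuller plan: the article includes its own analysis section, and other sections contradict it.

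Three stronger readings are tempting and are not supported.

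- *A reader might infer that three sections put the whole set of control variables in the primary models.* Two of them concern stress mindset alone. The third is an introductory sentence with an "or" that names no variable.
- *A reader might infer that the plan will adjust for post-intervention mindset.* No section says so. The Hypotheses section motivates the control role by pre-existing mindset and lists the outcome role separately, which points to Q1. Use of Q5 is a risk left open by the wording in Possible pitfalls, and it would bias the SAR estimate only if SAR moves mindset and mindset affects the outcome.
- *A reader might infer an error rate of 0.07 to 0.08 for every outcome.* That needs many covariates or a large R². For one four-item scale a smaller R² is the more natural assumption, and the repeated outcomes were not examined.

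**Conclusion.** The contradiction stands for stress mindset, with a looser general sentence pointing the same way and the role of SP left undefined. The article does not say which model decides H1 and H2, and it does not say outright which mindset measurement would be the covariate.

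The numerical consequence is modest. With one covariate, the type I error per test would be about 0.055 to 0.065 at an assumed R² of 1 to 10%, and about 0.08 only at an R² of 40% or with many covariates. These figures assume that the choice between models is really left open until both results are seen. The issue should be corrected because it affects which result counts, and because a careless correction could bring a post-intervention covariate into the SAR comparison. It does not undermine the design or the sample size.

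**What to change.** In the Statistical analysis plan section, name one model that alone decides H1 and H2. The preferable choice is SAR, WE and SAR × WE, plus gender (the stratification factor) and Q1 stress mindset, with the participant random effect kept for the repeated outcomes. This honours what Hypotheses and Possible pitfalls say about mindset. Keeping mindset out of the deciding model and correcting Hypotheses, Experimental session measures and Possible pitfalls would resolve the conflict equally well.

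In either case:

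- label every other covariate model a sensitivity analysis;
- state that Q5 mindset is an outcome and is not used as a covariate;
- flag that the DASS-21 and the ERQ, although meant as background measures, are answered at Q5 after the interventions and the task, so sensitivity models containing them need that caveat;
- align Hypotheses, Experimental session measures and both statements in Possible pitfalls, including the one on SP.

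The preferred option does add two named terms to the models as now written, so it is a small analysis decision as well as an edit. It needs no new data or participants, and step 2 of the working shows no meaningful loss of power from an uninformative covariate. The decision should be recorded before the outcome data are analysed.

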#### Cardiovascular measures

We will use two different devices to measure cardiovascular activity.

The Finometer ([name] Finapres Medical Systems, Amsterdam, The Netherlands) measures finger arterial pressure on a beat-to-beat basis by finger-cuff photoplethysmography. The finger cuff is wrapped around the middle phalanx of the left middle finger. Hydrostatic height correction of the finger with respect to the heart level will be active during the measurement. The Finometer produces waveform measurements similar to intra-arterial recordings and reconstructs brachial arterial pressure. The resulting artery pressure wave will provide systolic blood pressure (SBP), diastolic blood pressure (DBP), and mean arterial pressure (MAP). Data recorded by the Finometer will be analyzed using Beatscope software. The Finometer will be paused during the learning phase, to relieve participants from prolonged pressure.

The VU Ambulatory Monitoring System (VU-AMS, Free University, Amsterdam, The Netherlands) consists of seven non-invasive electrodes, which will be applied on the participants’ thorax and back. The instrument is used to obtain impedance cardiographic and electrocardiographic data, namely, HR, PEP, left ventricular ejection time, stroke volume (SV) and CO. Data will be analyzed using the VU Data Analysis & Management Software (VU-DAMS).

The parameters derived from the two instruments are used to calculate the cardiovascular index of challenge and threat (z-scored CO-TPR), which represents a primary outcome used for hypothesis testing. CO is calculated by multiplying SV by HR (CO = SV*HR). TPR is then obtained by dividing MAP by CO (TPR = MAP/CO). In line with standard procedures in research using the BPSM of challenge and threat, HR and PEP will be analyzed to ensure that the sample as a whole was sufficiently engaged [25, 87].

A motion sensor embedded in the VU-AMS will record triaxial acceleration and angular velocity to quantify body motion, which will be used as a control variable.

#### Salivary measures

A passive drooling method will be used to collect saliva into low-bind polypropylene 2 mL cryovials (Salicap, IBL International, Hamburg, Germany). Before taking a sample, participants will be asked to swallow all saliva in their mouth, then accumulate saliva for 2 min, and finally transfer all saliva into the Salicap. After collection, the samples will be stored in a freezer at -30 °C. Free salivary cortisol (sC) and dehydroepiandrosterone (sDHEA) will be measured using a Cortisol and Dehydroepiandrosterone Saliva Luminescence Immunoassay kit (IBL-Tecan, Hamburg Germany), respectively. Salivary alpha amylase (sAA) activity will be measured using reagents provided by DiaSys Diagnostic Systems (Holzheim, Germany). Both the anabolic balance (sDHEA divided by sC) and sAA are primary outcomes used for hypothesis testing.

#### Self-reported demands and resources

Before the learning phase (Q2) and before the BBN task (Q3), we will assess perceived demands with the question “How demanding do you expect the BBN task to be?” and resources with the question “How able are you to cope with the demands of the BBN task?”. After the task (Q4), participants will report how they perceived the demands by answering the question “How demanding was the BBN task?” and their resources with the question “How able were you to cope with the demands of the BBN task?”. Participants will be asked to rate each item on a 6-point Likert scale, ranging from 1 “not at all” to 6 “extremely”. The items are adapted to the context of the BBN task from previous research [37, 88, 89]. The resources-demands differential (i.e., resource score minus demand score) represents a primary outcome used for hypothesis testing. Higher scores indicate more perceived resources compared to demands and therefore more challenge-oriented stress responses.

#### BBN-skills performance

Participants’ skills performances as shown during the BBN encounter will be scored by three independent raters based on video recordings. Raters will be trained on an adapted version of the SPIKES scale (see supplementary material) [90] and the ‘global Breaking Bad News Assessment Scale’ (glBAS) [91]. The adapted SPIKES scale contains one item for the steps Setting, Knowledge, Emotions, Strategy & Summary and two items for Perception and Invitation (for these two steps, the mean of the two items will be used). An additional item assesses non-verbal communication aspects. All items are rated on a bipolar five-point rating scale ranging from 1 to 5 (the higher the better). The glBAS contains 5 items [91]. Each item represents different domains of BBN and is rated on a 5-point Likert scale ranging from 1 “very good” to 5 “very poor”. We will reverse the values of the original glBAS items to match the SPIKES scale. For the SPIKES scale, the final score is the grand mean of all steps and the non-verbal communication item across the three raters. Each step as well as the non-verbal item will be weighted equally. For the glBAS, the final score will be the grand mean across the 5 items and three raters. Communication performance is a primary outcome used for hypothesis testing.

The raters’ training will be structured according to previous research [90] and given by [name]. During approximately three days of training, raters will be presented with an introduction to BBN and critical literature, and the assessment methods will be discussed. Raters will then independently score video examples covering low, mediocre, and high student BBN-related performances by using the two scales. Each evaluation run will be followed by a group discussion during which raters are requested to reach a consensus on evaluation results.

#### Mood

We will use the MDMQ short-scale [92, 93] to assess three dimensions of mood, following the conceptualization of Matthews et al. [94] and Schimmack et al. [95]: valence (bad/good), calmness (tense/calm), and energetic arousal (tired/awake). Valence and calmness are composed of 3 bipolar items each, whereas energetic arousal is measured by 2 items. The scale ranges from 1 to 8 with two opposing adjectives as anchors (e.g., “Right now I feel tired (1) / awake (8)”). The total score for valence and calmness ranges from 3 to 24, and for energetic arousal from 2 to 12. Half of the items are reverse scored. For the individual dimensions, higher scores represent more positive valence, higher calmness, and higher energetic arousal. Mood is a secondary outcome analyzed for exploratory purposes.

#### Stress mindset measure

To gauge the extent to which participants perceive stress as enhancing or debilitating, we will use a validated 4-item short version of the SMM [86]. We translated the items to German and conducted a back translation to control for quality (see supplementary material). Participants will rate each item on a 5-point scale ranging from 0 “strongly disagree” to 4 “strongly agree”. Half of the items are reversed, and the mean is calculated as index score. Higher scores correspond to a more stress-is-enhancing mindset. Stress mindset represents a control variable and secondary outcome used for exploratory analyses.

#### Depression, anxiety and stress

The DASS-21 [96, 97] measures the three emotional states depression, anxiety, and stress with 7 items each (total of 21 items). Participants indicate how each of the items applied to them over the past week. The scale ranges from 0 “Did not apply to me at all” to 3 “Applied to me very much or most of the time”. Scores are calculated for each of the three subscales. For each subscale, higher scores stand for a higher manifestation of the emotional state. The German version of the test possesses good psychometric properties [97]. Depression, anxiety, and stress will be treated as control variables.

#### Emotion regulation

We will assess participants’ habitual use of the two emotion regulation strategies expressive suppression (4 items; e.g., “I keep my emotions to myself”) and cognitive reappraisal (6 items; e.g., “When I want to feel more positive emotion (such as joy or amusement), I change what I’m thinking about”) in their daily life with the German version of the ERQ [98]. Each item is rated on a scale ranging from 1 “not at all” to 7 “completely”. The mean is calculated separately for each emotion regulation strategy. Participants’ habitual use of expressive suppression and cognitive reappraisal will be used as control variables.

